### Treatment as usual (control) condition

Patients assigned to the control condition will receive TAU without SMS text messages. This will vary for each patient but usually consists of hospital and/or community mental health contact with the presenting individual, typically within 24-h of their hospital presentation, and a follow-up program of care including clinical reassessment, appropriate mental health services, drug and alcohol services and/or general practitioner follow-up and indicated psychological therapies.

### Outcome measures

As primary endpoints, we will assess at 6 and 12-months post-index discharge, i) the number of hospital DSH re-presentations in each condition (repetition event rate) and ii) the time to first re-presentation in each condition. Secondary end-points include i) any DSH re-presentation, ii) suicide mortality, and iii) all-cause mortality. Mortality data will be obtained from routinely collected data sources available through NSW Health, other government agencies, and the Centre for Health Record Linkage (CheReL).

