**Methods/design:**

Our study is a 24-month randomized controlled trial (RCT). Adult patients who present with DSH to hospital emergency, psychiatric, and mental health triage and assessment departments will be randomly assigned to an Intervention condition plus TAU receiving nine SMS text messages at 1, 2, 3, 4, 5, 6, 8, 10 and 12-months post-discharge. Each message will contain telephone numbers for two mental health crises support tele-services. Primary outcomes will be the difference in the number of DSH re-presentations, and the time to first re-presentation, within 12-months of discharge.

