### Sample size calculation

Assuming an incidence rate ratio (based on event rates) of RR = 0.66 [13] for the Intervention condition compared to TAU, with a 5% significance level, 80% power, and 10% adjustment for correlation of individuals within hospitals, a total sample size of 796 participants/subjects is required (398 participants in the Intervention condition and 398 subjects in the control condition). We have also assumed a median survival time (time to first repetition) in the TAU condition of 4.3 years. Currently ~ 15% in the usual care group who present for DSH re-present within the following 12-months, or a probability of survival of 0.85. Median survival (m) after 1-year (t) in the usual care group is t*log_e_(1/2)log_e_(*p* = 4.3 years). For assessing differences in median time to first repetition, assuming a median survival time in the usual care group of 73.5 days [12] and a similar relative difference in event rates between Intervention and TAU conditions as above (RR = 0.66), [13] the estimated median survival time in the Intervention condition is 121.8 days, which requires a total sample size of 138 participants/subjects (69 participants in the Intervention condition and 69 subjects in the TAU condition), with 5% significance and 80% power, and 10% adjustment for correlation of individuals within hospitals. The number of patients likely to die within the study period is very small. A previous longitudinal study in a similar Australian hospital setting [12] found a 1% suicide rate after 24 months and nearly a 2% suicide rate after 5 years.

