### Statistical methods

Participant/subject characteristics will be summarized using mean, standard deviation, median and inter-quartile range. Categorical variables will be summarized using frequencies, percentages and 95% confidence intervals. Means will be compared between the Intervention condition and TAU condition using the t-test or Mann-Whitney test. Comparisons of proportions between conditions will be performed using the Chi square test or Fisher’s exact test, as appropriate. Differences in the incidence of subsequent DSH between the Intervention and TAU conditions at 6 and 12 months will be investigated using multi-level negative binomial regression models (individuals nested within hospitals) to estimate the incidence risk ratios (IRR) and absolute risk differences based on incidence proportions in an intention to treat analysis. Adjustment for potential confounders identified from descriptive analyses will also be included in multivariate regression models as appropriate.

Relative differences in time to first subsequent DSH event between Intervention and control conditions at 6 and 12 months will also be investigated using multi-level Cox proportional hazard regression models (individuals nested within hospitals) to estimate hazard ratios (HR), with adjustment for potential confounders as appropriate. Kaplan-Meier survivorship functions and clustered log-rank tests will also be calculated to assess differences between Intervention and TAU conditions, with median time to first DSH event compared for Intervention and TAU conditions.

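### Six months is a primary time point in Outcome measures but not in the Abstract, and the stated 80% power does not cover it

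*Protocol article*

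**What the plan says.** Outcome measures: "As primary endpoints, we will assess at 6 and 12-months post-index discharge". The two endpoints listed are the number of re-presentations and the time to the first. Statistical methods follows this. It models "Differences in the incidence of subsequent DSH between the Intervention and TAU conditions at 6 and 12 months" by negative binomial regression, and time to first event by Cox regression at the same two times.

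The Abstract (Methods/design) differs. It gives the primary outcomes as the number of re-presentations and "the time to first re-presentation, within 12-months of discharge", with no 6-month time point.

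Sample size calculation holds two calculations, and neither mentions 6 months.

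- The first begins "Assuming an incidence rate ratio (based on event rates) of RR = 0.66", continues "with a 5% significance level, 80% power, and 10% adjustment for correlation of individuals within hospitals", and concludes that "a total sample size of 796 participants/subjects is required". Its control rate is dated: "Currently ~ 15% in the usual care group who present for DSH re-present within the following 12-months". That rate is converted to a median of 4.3 years.
- The second sizes time to first repetition from medians of 73.5 and 121.8 days and arrives at 138 patients.

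**The concern.** A power statement printed without a horizon, beside endpoints that are primary at two times, invites the reader to apply it to both. Fewer events have accrued at 6 months than at 12, so for the same relative effect the 6-month test is the weaker one. If the assumed effect of 0.66 is true, a 6-month primary test could well be non-significant. It would then be reported as a failed primary endpoint, or as conflicting with the 12-month result. The disagreement with the Abstract also leaves open which result decides the trial. The concern is about power and labelling, not multiplicity: it holds even if each time point is tested at the full 5%.

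**Working it through.** **Inputs from Sample size calculation.** Ratio 0.66, so |ln 0.66| = 0.4155; 398 per arm; 15% of TAU re-presenting by 12 months; 10% clustering adjustment, applied by dividing events by 1.1. Sidedness is not stated; two-sided 5% is assumed.

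**The plan's own figures.**
- The 4.3-year median reproduces: ln(0.5)/ln(0.85) = 4.27 years. This conversion assumes a constant hazard, λ = -ln(0.85) = 0.1625 per year.
- 138 reproduces: hazard ratio 73.5/121.8 = 0.603, Schoenfeld formula, 24-month accrual plus 12 months, × 1.1 = 137.7.
- 796 does not reproduce over a fixed 12-month window. About 182 events are needed (Schoenfeld; 188 by Freedman). This gives 1,446-1,494 patients before the 10% adjustment and 1,591-1,660 after. Following patients for up to 3 years without inflation comes within 3% (786-809).

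**Time to first re-presentation, constant hazard, N = 796.** Power = Φ(√d/2 × 0.4155 - 1.96), where d is the number of first events.

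| Horizon | TAU | Intervention | d | Power | Power with d/1.1 |
|---|---|---|---|---|---|
| 12 months | 15.0% | 10.2% | 100.2 | 55% | 51% |
| 6 months | 7.8% | 5.2% | 51.8 | 32% | 30% |

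The 6-month proportions are 1 - exp(-0.1625 × 0.5) and 1 - exp(-0.66 × 0.1625 × 0.5). A two-proportion test gives 31-33% at 6 months and 55-59% at 12. With a one-sided 5% test, 6-month power is Φ(1.495 - 1.645) = 44%, or Φ(1.426 - 1.645) = 41% with the adjustment.

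**Granting the full 80% at 12 months.** This corresponds to 1.96 + 0.84 = 2.80 standard errors. Half the events give 2.80/√2 = 1.98, and Φ(1.98 - 1.96) = 51%. Likewise, at the roughly 1,590 patients that would give 80% at 12 months with the adjustment, 6-month power is 52%.

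**Using the 73.5-day median.**
- As a whole-arm median with constant hazard, 1 - 2^(-365.25/73.5) = 97% re-present by 12 months, against 15% in the same section.
- As the median among those who repeat within a year (an assumption), about 84% of 12-month events fall in the first 6 months. Then d = 100.2 × 0.836 = 83.7 and power is 48%, or 44% with d/1.1. If 12-month power were truly 80%, this pattern would give Φ(2.80 × √0.836 - 1.96) = 73%.

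**Count endpoint.** The document gives neither events per patient-year nor dispersion, so both are assumed: TAU rate 0.15-0.50 per year, dispersion k from 0 to 4. The Wald test on the log rate ratio has variance [(1/μ0 + k) + (1/μ1 + k)]/n, with μ the expected 6-month count per patient and n = 398 or 362 per arm.
- Lowest: rate 0.15, k = 4, n = 362: variance (13.33 + 20.20 + 8)/362 = 0.1147; power Φ(0.4155/0.339 - 1.96) = 23%.
- Highest: rate 0.50, k = 0, n = 398: variance (4 + 6.06)/398 = 0.0253; power Φ(0.4155/0.159 - 1.96) = 74%.

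**The case against.** A reader might infer that the sizing rests on the 12-month rate alone, that half the window halves the events, and that both 6-month primary tests therefore have 30% power instead of 80%. The documents do not support this, for four reasons.

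- **A second sizing input exists.** Time to first repetition is sized separately from a 73.5-day median. Taken at face value, that gives over 99% power at 6 months with 796 patients. The objection stands against any claim that the 12-month rate is the only input. It does not rescue the 6-month endpoint, because a 73.5-day whole-arm median cannot coexist with 15% at 12 months.
- **Halving the events does not produce 30%.** It takes a true 80% to about 51%. The rest of the fall comes from 796 giving only 51-55% at 12 months under the same inputs, which is a separate fault. This stands.
- **The hazard may be highest soon after discharge.** This is plausible and raises the figures to 44-48%, or to 73% if 12-month power is granted as 80%. Both remain below 80%.
- **The 30% applies to first events only.** It cannot be asserted for the count test, whose event rate and dispersion are not given. This stands.

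Nor does the protocol expressly claim 80% at 6 months; the figure simply carries no horizon. And a fuller analysis plan may exist, but it would not remove the disagreement between the Abstract and Outcome measures in the published text.

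**Conclusion.** The concern holds in a limited form. Six months is primary in Outcome measures and analysed as such in Statistical methods. It is absent from the Abstract's primary window and not covered by the power statement.

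For time to first re-presentation, the best-supported figures are about 51% (12-month power truly 80%, even accrual) and about 30-32% (796 patients, 15% at 12 months, constant hazard, two-sided 5%). For the count endpoint only a range can be given, 23-74%, and it depends on the assumed rates. With no overdispersion and no clustering adjustment, 80% at 12 months needs 0.287 events per patient-year, so 80% at 6 months would need 2 × 0.287 = 0.574, above the range examined. Every scenario examined that is compatible with 15% at 12 months falls below 80% at 6 months. A single 30% for both tests, or blaming the whole fall from 80% on the shorter window, would overstate the case.

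**What to change.** 1. In Sample size calculation, state that the power figure refers to the 12-month horizon.
2. In Outcome measures and Statistical methods, follow the Abstract: make 12 months the primary time point for both endpoints, and report the 6-month analyses as secondary estimates with 95% confidence intervals.
3. If 6 months is to stay primary, amend the Abstract to match. Print the 6-month power for each endpoint with its assumptions: the hazard shape for time to first event, and the event rate and dispersion for the count.
4. Reconcile the 4.3-year and 73.5-day medians by saying which population each describes.

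The change costs wording only, with no extra patients or data. The downside is that 6 months loses its primary label or, if it keeps it, that a less favourable power is printed. Keeping 6 months primary at a real 80% would be a different matter: under the 15% constant-hazard input, time to first event needs about 2,790 patients (182 events / 0.0651 average 6-month risk), or about 3,070 with the 10% adjustment. Correcting the 796 itself is a separate task that these edits do not accomplish.

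### Two primary endpoints at two time points with no lead: if any one significant result counts, the false-positive chance is about 10% to 12%, against 5% per test

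*Protocol article*

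**What the plan says.** All references are to the protocol article.

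- **Outcome measures:** "As primary endpoints, we will assess at 6 and 12-months post-index discharge, i) the number of hospital DSH re-presentations in each condition", followed by "ii) the time to first re-presentation in each condition". Both endpoints are primary, and both are assessed at both times.
- **Statistical methods:** for the counts, "Differences in the incidence of subsequent DSH between the Intervention and TAU conditions at 6 and 12 months will be investigated" with multi-level negative binomial regression. For the second endpoint, the multi-level Cox model covers "Relative differences in time to first subsequent DSH event between Intervention and control conditions at 6 and 12 months".
- **Sample size calculation:** the calculation based on event rates is made "with a 5% significance level, 80% power, and 10% adjustment for correlation of individuals within hospitals". The separate calculation for time to first repetition uses 5% and 80% again, so the 5% is not divided between the endpoints.
- **Aims and hypotheses:** two separate hypotheses, event rate first and time to first re-presentation second. Neither is tied to a time point, and neither depends on the other.
- **Abstract, Methods/design:** the primary outcomes are the number of re-presentations "and the time to first re-presentation, within 12-months of discharge". Six months is not mentioned.

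No section says which comparison decides the trial, or whether one, some or all must succeed.

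**The concern.** Two endpoints at two times give four between-arm comparisons with primary status. The Abstract supports two. Nothing in the article settles what happens if they disagree, for example if the event rate differs at 6 months but not at 12.

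Disagreement is plausible. The Background section reports that a meta-analysis of brief contact interventions found a significant benefit for repetition event rates but a non-significant one for any repeat episode. Time to first re-presentation is close in content to the latter. The Abstract says that positive findings would support adoption by mental health services, so what counts as positive should be fixed before the data are seen.

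**Working it through.** **Figure to reproduce.** The article gives no overall error rate, so there is none to reproduce. Its 398 per arm is taken as given; whether 796 follows from its stated inputs is a separate question and does not affect the error rate.

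**Inputs from the article.** Two endpoints and two time points (Outcome measures); 5% for each endpoint, sidedness not stated and taken as two-sided (Sample size calculation); 398 per arm; about 15% of usual-care patients re-presenting within 12 months.

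**Inputs that must be assumed.** Events per person, dispersion and the timing of events. With gamma-Poisson counts of mean m and dispersion k, the proportion with any event is 1 − (1 + km)^(−1/k). Setting this to 0.15 gives m = (0.85^(−k) − 1)/k:

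- k = 1: (1.176 − 1)/1 = 0.18 events per person-year
- k = 4: (1.916 − 1)/4 = 0.23
- k = 8: (3.670 − 1)/8 = 0.33

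**Step 1: limits without simulation.** If the four tests were perfectly correlated, the chance of at least one false positive would be 5%. If they were independent, it would be 1 − 0.95^4 = 18.5%, and the Bonferroni bound is 4 × 5% = 20%. For two independent tests it is 1 − 0.95^2 = 9.75%. The real tests lie between, because the 6-month data are part of the 12-month data and a first event also enters the count.

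**Step 2: simulation under no effect.** Each run has 398 per arm. The tests are a log rate ratio with empirical (robust) variance and a log-rank test, each at 6 and 12 months. Three separate sets were run:

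| Any event by 12 months | Dispersion | At least one of four p < 0.05 | At least one of the two 12-month tests |
|---|---|---|---|
| 15% (4,000 runs per value) | 1 to 8 | 9.6% to 11.8% | 5.5% to 8.7% |
| 15% | 1 to 8 | 10.9% to 12.0% | 7.0% to 8.6% |
| 16% to 20%, event timing also varied (6,000 runs per scenario) | 1 to 6 | 10.9% to 12.2% | about 7% to 8% |

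In the first set the any-of-four rate was 9.6% at k = 1, 11.5% at k = 4 and 11.8% at k = 8, and each single test rejected in 4.3% to 5.5% of runs. In the third set the pairwise correlations were about 0.68 to 0.96. Calibrating each test there to exactly 5% gave 10.9% to 11.3%, so the excess comes from the number of tests and not from poorly sized ones. Counting only false findings of benefit gave about 5.5% to 6.0%, against 2.5%.

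**Step 3: size of the excess.** 9.6/5 = 1.9 and 12.2/5 = 2.4, so the any-of-four rate is roughly double the per-test level.

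**Step 4: what an alpha split would cost.** The sample size scales with (z for alpha + z for power)². At 5% two-sided and 80% power this is (1.960 + 0.842)² = 7.85.

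- Four tests at 1.25% each: (2.498 + 0.842)² = 11.15. The ratio is 1.42, and 796 becomes about 1,131. Kept at 796, a nominal 80% power falls to about 62%.
- Two tests at 2.5% each: (2.241 + 0.842)² = 9.51. The ratio is 1.21, and 796 becomes about 964, or power falls to about 71%.

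**The case against.** **Multiplicity rules are usually left to the SAP, and this is a condensed article.** This stands in part: the lack of an adjustment is not in itself a finding. But the article itself declares two endpoints primary at two times and gives a different window in its Abstract. An SAP could add an adjustment, but it would not remove that mismatch.

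**The stated 5% is kept.** A reader might infer that the trial fails to control the error rate it states. The article does not support that. Its 5% belongs to each sample size calculation, no family-wise rate is promised, and each simulated test holds about 5%. Asking for an overall rate is a reasonable standard for a confirmatory trial, but it is not one that the article sets for itself.

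**No rule says that one success is enough.** Correct. A reader might infer that any of the four may be reported as a positive trial; the article neither says so nor requires all to succeed. The 10% to 12% is therefore conditional on that reading.

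**Six months may be a question of its own.** It would be tempting to call the 6-month analyses the same data cut short. But the Intervention section sends messages monthly to month 6 and then only at months 8, 10 and 12, so an effect during monthly contact is a legitimate question. It is a reason to keep the analyses, not to leave their rank open.

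**The Abstract may be shorthand, and a lead is hinted at.** Six months falls within 12, and the event rate is both hypothesis 1 and the first-listed endpoint. A hint is not a rule, though, and it says nothing about the time point.

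**The simulation is simplified.** It does not use the planned multi-level models, and hospital clustering and the first/subsequent strata are not represented. The percentages are approximate.

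**Conclusion.** The concern holds in a limited form. The article fixes four primary comparisons with no lead endpoint, lead time point, order or alpha split, and its Abstract and Outcome measures section differ on the time frame. If any one significant result is treated as primary success, the chance of at least one false positive is about 10% to 12%. On the Abstract's two 12-month comparisons it is about 5.5% to 9%. The independence figure of 18.5% would overstate the problem.

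These sizes rest on two-sided 5% tests, about 15% to 20% of patients with any event, dispersion 1 to 8 and simplified tests. The any-of-four result was stable over those ranges.

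**What to change.** Align the Abstract, Outcome measures and Statistical methods sections as follows:

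1. The primary endpoint is the number of re-presentations at 12 months (hypothesis 1), tested at 5%.
2. Time to first re-presentation at 12 months (hypothesis 2) is tested at 5% only if the first test is significant.
3. Both 6-month analyses are secondary.

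This order keeps the overall error for the two hypotheses at 5%. If hypothesis 1 has no true effect, any false claim must first pass its 5% test. If it has one, only the 5% test of hypothesis 2 can err.

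The change is one of wording. The 796 is unaffected, and hypothesis 1 keeps the full 5%. The cost is that hypothesis 2 alone, or a 6-month result, can no longer be claimed as primary success. If the sponsor is unwilling to give that up, an alpha split or a requirement that both endpoints succeed would also settle the matter. A split costs sample size or power as shown above, and requiring both lowers the chance of overall success.

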### Sample size calculation

Assuming an incidence rate ratio (based on event rates) of RR = 0.66 [13] for the Intervention condition compared to TAU, with a 5% significance level, 80% power, and 10% adjustment for correlation of individuals within hospitals, a total sample size of 796 participants/subjects is required (398 participants in the Intervention condition and 398 subjects in the control condition). We have also assumed a median survival time (time to first repetition) in the TAU condition of 4.3 years. Currently ~ 15% in the usual care group who present for DSH re-present within the following 12-months, or a probability of survival of 0.85. Median survival (m) after 1-year (t) in the usual care group is t*log_e_(1/2)log_e_(*p* = 4.3 years). For assessing differences in median time to first repetition, assuming a median survival time in the usual care group of 73.5 days [12] and a similar relative difference in event rates between Intervention and TAU conditions as above (RR = 0.66), [13] the estimated median survival time in the Intervention condition is 121.8 days, which requires a total sample size of 138 participants/subjects (69 participants in the Intervention condition and 69 subjects in the TAU condition), with 5% significance and 80% power, and 10% adjustment for correlation of individuals within hospitals. The number of patients likely to die within the study period is very small. A previous longitudinal study in a similar Australian hospital setting [12] found a 1% suicide rate after 24 months and nearly a 2% suicide rate after 5 years.

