### Participants/Subjects

For the purpose of this study, participants will be defined as patients who have randomly been allocated to the Intervention condition and provide their informed consent to receive text messages. Subjects will be defined as patients who are randomly allocated to the TAU condition and do not receive text messages. To be eligible for study inclusion, patients must be: assessed at an emergency department (ED) after presenting with DSH; at least 16-years old; competent in reading and understanding English; and have a mobile phone. Patients will be excluded from the study if they: refuse to participate; do not have a mobile phone; do not have a fixed Australian address or are otherwise unable to provide informed consent.

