### Procedure

The usual treating health and mental health clinicians (Psychiatrists, Clinical Nurse Consultants, Registered Nurses and Psychiatry Registrars) will assess patients at EDs, Toxicology Centers, Psychiatric Emergency Care Centers, and Mental Health Triage and Assessment Centers. Clinicians will enroll eligible patients into the Intervention or TAU conditions and record the name, Medical Record Number, mobile phone number and date of birth of participants/subjects on Allocation Information Sheets. Envelopes will be supplied at study commencement, including at least 500 green envelopes (numbered for first DSH presentation) and at least 500 blue envelopes (numbered for subsequent DSH presentation). Allocation Information Sheets will be concealed inside sealed envelopes and the allocating clinician will draw the next numbered envelope for each participant/subject form the appropriate stratification. Demographic information will be collected by hospital administration staff when patients first present to the ED.

Figure 1 outlines the methodological process that will be followed for the SMS SOS Study. Allocation will occur via numbered sealed envelopes. Upon enrolling patients into the study, health professionals will attach a patient identification label (which includes the patient’s name, gender, date of birth and Medical Record Number) to an Allocation Information Sheet, which would be drawn from a selected envelope. For patients allocated to the Intervention condition, clinicians will explain that they may receive text messages for up to 12-months post discharge. Clinicians will provide patients in the Intervention condition with a Participant Information Sheet and they will obtain written consent. To reduce unnecessary patient burden, patients allocated to the control condition (TAU) will not be recruited by clinicians, as per the Zelen single-consent design [11].

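### The sample size makes no allowance for refusal after allocation, so the stated 80% power does not carry over to an intention-to-treat comparison unless the ratio 0.66 is already an as-allocated effect

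*Protocol article*

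**What the plan says.** All references are to the protocol article.

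- **Sample size calculation.** The event-rate endpoint is sized as follows: "Assuming an incidence rate ratio (based on event rates) of RR = 0.66 [13] for the Intervention condition compared to TAU". Significance is set at 5% and power at 80%, and the number is raised by 10% because patients are clustered by hospital. The total is 796, given as "398 participants in the Intervention condition and 398 subjects in the control condition". The hospital adjustment is the only inflation mentioned.
- **Participants/Subjects.** The term used in that count is defined: "participants will be defined as patients who have randomly been allocated to the Intervention condition and provide their informed consent to receive text messages". Patients allocated to treatment as usual (TAU) are called *subjects*. The same section excludes from the study patients who refuse to take part.
- **Randomization, allocation, and materials; Procedure.** Patients are randomised first, under a Zelen single-consent design. Consent comes afterwards and in one arm only: "Clinicians will provide patients in the Intervention condition with a Participant Information Sheet and they will obtain written consent". Control patients are not approached.
- **Statistical methods.** The negative binomial models are to give incidence ratios and "absolute risk differences based on incidence proportions in an intention to treat analysis". Nothing is said there about patients who decline after allocation to the Intervention.

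**The concern.** In this design a refusal after allocation can arise only in the Intervention arm, because nobody in the control arm is asked. A patient who declines receives no messages and is in effect treated as a control. An ITT analysis in its ordinary meaning keeps that patient in the Intervention arm, which pulls the observed rate ratio towards 1. Nothing in the sample size covers this.

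The figure 398 is also ambiguous. By the article's definition it counts consenters in one arm and everyone allocated in the other. With equal random allocation, those two counts can both be 398 only if almost nobody refuses.

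At stake is the meaning of the 80%. If refusal is appreciable, a null ITT result could reflect messages not received as much as messages that do not work. The trial would be read as adequately powered when it was not.

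**Working it through.** **Inputs from the article.** Rate ratio 0.66; 5% significance (two-sided assumed, as the article does not say); 80% power; 398 per arm; inflation of 1.10 for hospitals; 12-month TAU repetition risk from "Currently ~ 15% in the usual care group who present for DSH re-present within the following 12-months".

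**Inputs assumed.** Refusal fraction q among patients allocated to the Intervention (the article gives none; 5% to 30% shown). Refusers have the same baseline rate as other patients and gain no benefit. The ratio 0.66 is the effect in consenters.

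**Step 1. The plan's own figure.** The total of 796 does not follow from the printed inputs. Comparing 15% with 0.66 × 15% = 9.9% as two proportions needs 1,445 in total after the 10% inflation. A Poisson rate comparison at 0.15 events per year needs 1,677. A total of 796 corresponds to an unstated TAU rate of about 0.32 events per year (Poisson), or 0.42 (negative binomial with dispersion 1). That is a separate matter. The steps below take the article's claim at face value, so that 398 per arm gives exactly 80% at 0.66.

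**Step 2. Dilution.** RR_ITT = q + (1 − q) × 0.66. At q = 0.10 this is 0.10 + 0.90 × 0.66 = 0.694.

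**Step 3. Power with the number allocated fixed at 398 per arm.** At 80% power the standardised effect is 1.960 + 0.842 = 2.802. With the standard error held constant, it becomes 2.802 × ln(RR_ITT) / ln(0.66), and power = Φ(that value − 1.960). At q = 0.10: 2.802 × (−0.3653) / (−0.4155) = 2.463, and Φ(0.503) = 0.692. A second calculation lets the variance change with the Intervention event rate (Poisson, and negative binomial with dispersion 1).

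| q | RR_ITT | Power, constant standard error | Power, variance changing with rate | Total N for 80% (changing variance) |
|---|---|---|---|---|
| 5% | 0.677 | 74.9% | 75–76% | about 890 |
| 10% | 0.694 | 69.2% | 70–71% | 1,000–1,008 |
| 20% | 0.728 | 57.2% | 59–60% | 1,288–1,308 |
| 30% | 0.762 | 44.9% | 47–48% | 1,712–1,748 |

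**Step 4. Power if 398 means consenters.** With equal allocation, both arms grow to 398/(1 − q) before 398 have consented: about 442 per arm at 10%, 498 at 20% and 569 at 30%. The standardised effect from Step 3 is divided by √(1 − q). At q = 0.10: 2.463 / √0.90 = 2.596, and Φ(0.636) = 0.738.

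| q | Power, constant standard error | Power, variance changing with rate |
|---|---|---|
| 10% | 74% | 75% |
| 20% | 67% | 69% |
| 30% | 59% | 62–63% |

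On either reading of 398, ITT power is below 80% at every refusal fraction above zero.

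**The case against.** Four points on the other side deserve weight.

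1. **The article does not say that refusers are analysed.** A reader might infer that the plan powers one group and analyses another. That is not established: the Statistical methods are silent on refusers, and the eligibility text excludes patients who refuse. If that exclusion governs, the powered and analysed groups match, and the fault is a post-randomisation exclusion in one arm only, which is not ITT. This stands against the stronger reading. It does not remove the need to act, because the two passages cannot both hold under consent after allocation.

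2. **The ratio may already be diluted.** The article attaches 0.66 to the Intervention condition against TAU, which reads naturally as a contrast between allocated arms. If the cited source estimated it as allocated, with similar refusal, the loss is smaller or absent. The article does not say. This stands as a condition on the conclusion.

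3. **The term is used loosely.** Elsewhere *participants/subjects* are stratified and drawn an envelope before allocation or consent, and equal arms suit a count of randomised patients. So 398 may well mean patients allocated. That moves the calculation from Step 4 to Step 3, where the loss is larger.

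4. **Missing secondary analysis.** A reader might also count it as an error that no effect in acceptors is planned. It is not one: an analysis plan that is not shown may hold it.

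**Conclusion.** The point holds in a conditional form. The sample size has no allowance for refusal, although the design makes refusal after allocation possible in one arm only and the analysis is named as ITT. The stated 80% is delivered under ITT only if nobody refuses, or if 0.66 is already an as-allocated ratio from a setting with similar refusal.

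Otherwise the loss is about 4–5 points at 5% refusal and 9–11 points at 10% with the number allocated fixed, and it grows quickly beyond that. If both arms are enlarged until 398 consent, the loss is about 5–6 points at 10% refusal.

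These sizes rest on an assumed refusal rate, on refusers having the same baseline rate and no benefit, and on taking 80% at 0.66 as the starting point. The documents do not support the flat statement that the power belongs to a group the plan leaves unanalysed. What they show is an unresolved conflict over refusers and a sample size that ignores them. This should be corrected; confidence in its practical size is medium.

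**What to change.** 1. State the sample size as 398 patients *allocated* per arm, and use one term for that count throughout.
2. Reconcile the exclusion of refusers in Participants/Subjects with the consent-after-allocation procedure and the ITT statement, so that Intervention patients who decline stay in the ITT analysis as allocated.
3. Say whether 0.66 is an as-allocated effect. If it is not, restate ITT power at RR_ITT = q + (1 − q) × 0.66 for a stated range of q.
4. Optionally, add a complier-average estimate with allocation as the instrument, as a secondary analysis. It needs consent status and refusers' outcomes to be recorded; the Data collection list names neither consent status nor message receipt. Its interval would be wider than that of the ITT estimate, and it assumes that allocation acts only through the messages.

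Items 1 to 3 cost a few sentences and a less favourable stated power. If the sponsor wishes to keep 80% under ITT, the cost is recruitment: about 1,000 patients in total at 10% refusal, against 796.
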